### Outcome

The primary outcome measure used in this trial will be the lower extremity section of Fugl Meyer (FM) Assessment [26]. The FM is considered by many in the area of stroke rehabilitation to be one of the most inclusive quantitative measures of sensorimotor impairment following stroke and its use has gained international acceptance as a feasible and appropriate clinical and research tool for evaluating changes in motor impairment following stroke [27]. Excellent intra-rater and inter-rater reliability and construct validity have been demonstrated [28,29].

A series of secondary outcome measures will also be used to evaluate participants' recovery including the Motor Assessment Scale [30], the Berg Balance Scale [31], the Six Minute Walk Test [32] the Barthel Index [33], the Reintegration to Normal Living Index [34] and the Nottingham Extended Activities of Daily Living Index [35].

The Caregiver Strain Index [36], a 13-item self-report measure designed to measure strain relating to care provision, will be administered to the nominated 'family member/friend' of the person with stroke. In addition, a semi-structured interview will take place with each participant and their nominated 'family member/friend' individually, in relation to their experience of the exercise therapy programme. A physiotherapist unknown to the participant will conduct interviews. All interviews will be audio recorded.

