### Power

Sample size is based on a power analysis. A sample size calculation was performed for the primary outcome variable, which is the lower extremity section of the Fugl-Meyer (FM). For the FM lower extremity, a change of greater than five points reflects a change greater than measurement error [42]. Power calculations indicate that a total of 40 participants are needed in order to detect with 80% power a difference of 20% between the groups at a significance level of 5%. It is anticipated that it will take 18–24 months to recruit the required number of participants.

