### Analysis

All data will be collected on paper and the records will be stored by registration number in a secure cabinet. Anonymised data will be transferred to a computer database and secured using a password. An independent researcher will cross check all entries. Appropriate statistical tests will be carried out on the data using MINITAB Release 13.1.

The statistical analyses will be performed according to the 'intention to treat' principle and participants will be analysed in the group to which they were randomly assigned. Participants who withdraw from the experimental group but allow further data collection will have data collected. A 'last measurement carried forward' method is used to predict outcome in dropouts [43].

The purpose of the statistical analysis is to test the hypothesis that there will be a clinically significant difference in functional recovery between participants in the control group and the experimental group from baseline to post-intervention assessment. Firstly, the baseline scores of the participants' demographic, primary and secondary outcomes will be compared in the two groups. If necessary, adjustments for baseline variables will be made using analysis of covariance. Analyses will be carried out to examine the difference between the groups with respect to the change in the lower extremity FM test score from baseline to post-intervention assessment. Secondary outcomes will be compared between the two groups using Student's t-test or the Wilcoxon rank sum test for ordinal data. Descriptive statistics will also be used to represent demographic data.

All interviews will be tape recorded, transcribed and examined in terms of themes according to the method devised by Miles and Hubberman [44]. The responses from all participants to each question will be transferred to Microsoft Excel for examination. Following an examination of the responses to each question, a coding system will be developed in order to facilitate the identification of recurrent responses. Three researchers will be provided with the responses to all of the questions in an unencoded format; thereafter they will independently code the responses sequentially using the predefined codes. All coding disagreements will be resolved through discussion.

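### Baseline adjustment is left to an undefined judgement made after the arms are compared at baseline; the primary model should be fixed in advance as ANCOVA on baseline Fugl-Meyer

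*Protocol article*

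**What the plan says.** The primary outcome is named in the Outcome section: "The primary outcome measure used in this trial will be the lower extremity section of Fugl Meyer (FM) Assessment". The Analysis section then sets out a sequence.

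- First comes a look at balance: "Firstly, the baseline scores of the participants' demographic, primary and secondary outcomes will be compared in the two groups".
- Next comes a conditional step: "If necessary, adjustments for baseline variables will be made using analysis of covariance".
- The main comparison concerns "the change in the lower extremity FM test score from baseline to post-intervention assessment".

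The article does not say what makes adjustment necessary, which baseline variables would enter the model, or whether baseline FM is always among them. No other section fixes the primary model. The Power section states that "a total of 40 participants are needed" and that this number serves "to detect with 80% power a difference of 20% between the groups", but it does not tie the calculation to a change score or to an adjusted analysis.

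**The concern.** Allocation is by computer-generated random numbers, so any difference between the arms at baseline arises by chance. Comparing the arms therefore cannot show that adjustment is needed. The reason to adjust for baseline FM is that it predicts 8-week FM, and that holds whatever the observed balance.

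Two things are at stake.

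- **Discretion.** With no criterion and no covariate list, the model behind the main result is chosen after at least the baseline data have been seen. The text does not say whether outcome data would still be unseen at that point.
- **Precision.** When adjustment is not triggered, the analysis is an unadjusted change score. This imposes a slope of 1 on baseline instead of estimating it. In a trial of 40 patients the lost precision may matter.

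This is not a detail left to an unseen analysis plan. The article states a decision rule, and an analysis plan that followed it would inherit the weakness.

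**Working it through.** **The plan's own figure.** The total of 40 can be neither reproduced nor refuted. The Power section gives no SD, no base for the 20%, no sidedness and no correlation. Solving backwards for 20 per arm, two-sided 5% and 80% power gives a standardised difference of 0.886 by the normal approximation and 0.909 by the t-test. The second is used below to set the unadjusted change-score analysis at 80% power.

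**Inputs from the article.** Total 40, 80% power, 5% significance, change in lower extremity FM as the default comparison, conditional ANCOVA.

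**Assumed inputs.** Equal allocation (20 per arm), a two-sided test, normal data, correlation ρ between baseline and 8-week FM over a range, SD ratio k (8-week SD divided by baseline SD), and *necessary* read as p<0.05 on baseline FM alone. The article gives none of these.

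**Step 1: variance.** With the baseline SD set to 1:

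- change score: 1 + k² − 2ρk
- ANCOVA: k²(1 − ρ²)
- ratio, ANCOVA to change score: k²(1 − ρ²) / (1 + k² − 2ρk)

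For k = 1 the ratio reduces to (1 + ρ)/2, which is 0.75, 0.85 and 0.90 at ρ = 0.5, 0.7 and 0.8.

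**Step 2: power with equal SDs.** Simulation, 20 per arm, 200,000 trials per setting:

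| ρ | Change score | Conditional rule | Routine ANCOVA |
|---|---|---|---|
| 0.5 | 80% | 81% | 89% |
| 0.7 | 80% | 80% | 85% |
| 0.8 | 80% | 80% | 83% |

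The conditional rule stays close to the change score because, under the assumed trigger, it adjusts in only about 5% of trials.

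**Step 3: unequal SDs.**

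- ρ = 0.7, k = 0.8: 0.64 × 0.51 / (1 + 0.64 − 1.12) = 0.3264 / 0.52 = 0.63. ANCOVA power is about 94%.
- ρ = 0.7, k = 1.2: 1.44 × 0.51 / (1 + 1.44 − 1.68) = 0.7344 / 0.76 = 0.97. ANCOVA power is about 80%, practically no gain.
- ρ = 0.8, k = 1.25: 1.5625 × 0.36 / (1 + 1.5625 − 2) = 0.5625 / 0.5625 = 1.00. ANCOVA power is about 79% against 80%. There is no gain, because the best slope ρk equals 1 and the change score already uses it.

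**Step 4: imbalance that the trigger misses.** With 20 per arm, a 5% test flags a baseline difference only above 2.024 × √(2/20) = 0.64 SD. A chance difference of 0.5 SD gives t = 0.5/√0.1 = 1.58 and p of about 0.12, so it would go unadjusted. With k = 1 the expected change-score difference in such a trial is shifted by (1 − ρ) × 0.5 SD. As a share of the effect assumed in Step 2, 0.909 × √(2(1 − ρ)), this is about 28%, 21% and 17% at ρ = 0.5, 0.7 and 0.8. Over all randomisations the shift averages to zero.

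**Step 5: type I error, k = 1, same simulation.**

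| ρ | Fixed trigger (p<0.05) | Smaller of adjusted and unadjusted p |
|---|---|---|
| 0.5 | 4.4% | 7.3% |
| 0.7 | 4.6% | 6.8% |
| 0.8 | 4.7% | 6.4% |

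**The case against.** The strongest reply has four parts.

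1. **The trigger is not in the article.** It says only that baselines are compared; it mentions no test and no threshold. A reader might infer that about 95% of such trials would be analysed unadjusted. That holds only if the trigger is p<0.05 on baseline FM alone. The comparison also covers demographics and secondary outcomes. With FM and the six patient-level secondary outcomes, at least one of seven independent 5% comparisons would fire in 1 − 0.95⁷ = 30% of trials. This part stands: the 95% figure and the powers of the conditional rule are illustrations, not properties of the plan.

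2. **The gain needs roughly equal SDs.** Step 3 shows it can vanish. Entry is restricted to an Orpington score of 3.2 to 5.2, which could narrow the baseline spread, and the article gives no SD. This also stands, although the same uncertainty allows a larger gain.

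3. **A change score already uses baseline.** The loss is therefore partial: about 9, 5 and 3 power points in the central case. The 80% starting point is itself assumed. This stands.

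4. **Validity is not shown to fail.** A reader might infer that the rule inflates type I error or biases the result. Under a fixed trigger the error is slightly below 5%, and the change score is unbiased over randomisation. Inflation requires the analyst to choose by p-value. The wording leaves room for that, but nothing in the article says it is intended, and the sequence it describes starts from baseline data.

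None of this rescues the rule itself. It remains undefined, and observed balance remains the wrong ground for the decision.

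**Conclusion.** The concern holds in a limited form. The article conditions the primary model on an observed baseline comparison, without a criterion or a named covariate. That leaves the choice to discretion after data are seen, and it forgoes the usual precision gain from adjusting for baseline FM whenever adjustment is not triggered.

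With 20 per arm, equal SDs, 80% power for the change score and a p<0.05 trigger on baseline FM, the gain from always adjusting is about 3 to 9 power points for ρ between 0.8 and 0.5. It is larger if the 8-week SD is the smaller one, and nil at ρ = 0.8 with an SD ratio of 1.25. Type I error is a concern only if the open wording is used to select the more favourable analysis, when it reaches about 6% to 7%.

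The documents do not support calling this a demonstrated bias or a fault that invalidates the trial. It is something that should be fixed: a free improvement, not a condition for proceeding.

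**What to change.** Replace the conditional sentence in the Analysis section with a fixed rule. The primary analysis is ANCOVA of the 8-week lower extremity FM score on randomised group, with baseline FM as the pre-specified covariate, whatever the observed balance. Present baseline characteristics by arm descriptively only, and give that comparison no role in choosing the model.

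The Orpington score, already collected for eligibility, could be added as a second covariate. That is optional: its range is cut by the entry criteria, no calculation here supports a gain from it, and baseline FM alone answers the point.

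The cost is a sentence or two. ANCOVA is already among the planned methods, baseline FM is already measured, and no extra patients or data are needed. The change should be made before outcome data are seen.

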## Methods

### Study Design

A prospective single-blind randomised controlled trial will be conducted. Forty subjects will be randomised into either an experimental group or a control group using sealed, computer generated random numbers. The progression from screening and enrollment to randomisation is illustrated in Figure legend 1.

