### Blinding

An independent physiotherapist blinded to group allocation will assess all participants using the battery of outcome assessments on entry to the study, on completion of the eight-week trial and finally at the three month follow-up stage.

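### Secondary outcomes: unadjusted two-sample tests on an unstated scale, with baseline adjustment left to an undefined need, give up precision in a 40-patient trial

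*Protocol article*

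**What the plan says.** All of this is in the protocol article.

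- **Secondary tests (Analysis).** "Secondary outcomes will be compared between the two groups using Student's t-test or the Wilcoxon rank sum test for ordinal data". No baseline term is named, and neither is the scale of the comparison.
- **Baseline comparison and adjustment (Analysis, same paragraph).** As a first step, "the baseline scores of the participants' demographic, primary and secondary outcomes will be compared in the two groups". Then: "If necessary, adjustments for baseline variables will be made using analysis of covariance".
- **Primary outcome, for contrast (Analysis).** The groups are compared "with respect to the change in the lower extremity FM test score from baseline to post-intervention assessment". Here the scale is explicit.
- **Overall hypothesis (Analysis).** It concerns "functional recovery between participants in the control group and the experimental group from baseline to post-intervention assessment".
- **Availability of baseline scores (Blinding).** A blinded physiotherapist "will assess all participants using the battery of outcome assessments on entry to the study", and again at eight weeks and at the three-month follow-up.
- **Size (Study Design).** "Forty subjects will be randomised into either an experimental group or a control group".

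The Outcome section lists six secondary patient scales. It describes the Caregiver Strain Index separately, as given to the family member or friend, without stating when.

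**The concern.** A two-sample t-test or rank sum test has no place for a covariate. If post scores are compared, differences between patients that were already present at entry stay in the error term, and any chance baseline gap between two small groups passes partly into the estimated effect. If change scores are compared, baseline is used, but with a fixed coefficient of one instead of the coefficient the data support.

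The conditional ANCOVA sentence does not settle this. It follows a look at the baseline data and gives no rule for when adjustment is needed, so the analysis of each scale could be chosen after its imbalance is known. Observed imbalance is also a poor criterion, because the precision gain comes from the correlation between baseline and outcome and is there even when the groups balance well.

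The outcomes affected are close to the trial's purpose. The stated aim is functional recovery, whereas the Outcome section presents the primary Fugl-Meyer score as a measure of impairment. Function is measured largely by secondary scales such as the Barthel Index, the Berg Balance Scale and the Nottingham index.

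**Working it through.** **Inputs.** Total N = 40 (Study Design). I assume 20 per arm, because the ratio is not stated, and a two-sided 5% test. The baseline-to-outcome correlation r is not in the document, so I take 0.3, 0.5, 0.7 and 0.8. I also assume equal standard deviations at baseline and afterwards, and approximate normality.

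**The plan's own figure.** The Power section gives 40 participants for 80% power at 5% on the primary outcome. It gives no standard deviation and no base for its 20% difference, so the figure can be neither reproduced nor refuted. Solving backwards with the noncentral t, 20 per arm and 80% power imply a standardised difference of d = 0.909. I use this d only as a common starting point; the plan makes no power claim for secondary outcomes.

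**Variance of the treatment difference, relative to σ² × 2/n:**
- post-score test: 1
- change-score test: 2(1 − r)
- ANCOVA: 1 − r²

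So ANCOVA relative to post score is 1 − r², and relative to change score it is (1 − r²)/[2(1 − r)] = (1 + r)/2. Both are below 1 for every r between 0 and 1.

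**Power.** The noncentrality is d × √(n/2) = 0.909 × √10 = 2.87 for an unadjusted test with 80% power (38 df). For ANCOVA, d is divided by the square root of the variance ratio, with 37 df. At r = 0.7:
- against post score: 0.909/√0.51 = 1.273, power 97.5%
- against change score: 0.909/√0.85 = 0.986, power 85.9%

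| r | Variance cut vs post | ANCOVA power if post test has 80% | Variance cut vs change | ANCOVA power if change test has 80% |
|---|---|---|---|---|
| 0.3 | 9% | 83.5% | 35% | 93.5% |
| 0.5 | 25% | 89.8% | 25% | 89.8% |
| 0.7 | 49% | 97.5% | 15% | 85.9% |
| 0.8 | 64% | 99.7% | 10% | 83.9% |

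The two power columns start from different effects, each set so that its own unadjusted test has 80%, so they should not be compared with each other. Confidence intervals narrow by about 5%, 13%, 29% and 40% against post score, and by 19%, 13%, 8% and 5% against change score. At r = 0.5 the gain over either unadjusted test equals 40/0.75 ≈ 53 patients instead of 40.

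**Would a look at baseline imbalance catch what matters?** With 20 per arm the standardised baseline difference has standard deviation √(2/20) = 0.32. A gap of 0.5 SD or more therefore arises by chance on any one scale about 11% of the time. A gap of exactly 0.5 SD has t = 0.5/0.316 = 1.58 and p of about 0.12, so a 5% significance test at baseline would pass it. At r = 0.7 it would shift a post-score comparison by 0.7 × 0.5 = 0.35 SD, and a change-score comparison by (1 − 0.7) × 0.5 = 0.15 SD in the opposite direction.

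**The case against.** The strongest reply is that the plan already provides for baseline. The Analysis paragraph compares baseline scores, explicitly including the secondary outcomes, and then allows ANCOVA. The hypothesis is framed as recovery from baseline and the primary outcome is analysed as change, so change scores are a natural reading for the secondary outcomes too. On that reading the gain at r = 0.7 or 0.8 is modest: 80% to 86% or 84%. Randomisation makes the unadjusted tests valid, the trial is powered only on the primary outcome, and an article may leave such detail to a fuller document.

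Much of this stands. A reader might infer that the tests ignore baseline altogether, or cannot use it. The text does not support that: ANCOVA is mentioned and change scores are not excluded. The large gains against post scores hold only if post scores are what is compared.

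What does not stand is that the ANCOVA sentence cures the problem. It makes adjustment depend on observed imbalance, with no stated trigger. Nor is this only missing detail: the article names the tests and states a conditional rule, and both are weaker than an equally simple alternative.

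A reader might also see a multiplicity problem in the number of secondary scales. The document does not bear that out. One primary outcome is named and the trial is sized on it, no 5% level is stated for secondary tests, and no secondary test at follow-up is specified. A false-positive rate computed as if these overlapping scales were independent would overstate the risk.

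**Conclusion.** The point holds as one of efficiency and pre-specification, not of validity. The scale of the secondary comparison is not fixed, and baseline adjustment is left to a data-driven decision although the patient battery is measured at entry. Planned ANCOVA is more precise on either reading. Against change scores the variance saving is 10% to 35% over r = 0.8 to 0.3; against post scores it is 9% to 64% over r = 0.3 to 0.8. These sizes rest on an assumed r, 20 per arm and equal standard deviations before and after. Where a scale sits near its floor at entry, r may be low, and the gain over a post-score test would then be small. The Caregiver Strain Index falls outside the point unless it is measured at baseline, which the document does not state.

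**What to change.** Replace the secondary-outcome sentence, and the conditional adjustment as it applies to those outcomes, with a fixed rule. Each secondary patient scale is analysed by ANCOVA of the post-intervention score on treatment group and that scale's own baseline score, whatever baseline imbalance is seen. A rank-based ANCOVA or a proportional-odds model with baseline is used for ordinal or floor-limited scales, with the choice for each scale named in advance. Report adjusted differences with 95% confidence intervals (for a proportional-odds model, the adjusted odds ratio with its interval). Apply the same rule to the Caregiver Strain Index only if it is collected at baseline.

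This also settles the change-or-post question, because ANCOVA with the baseline score as covariate gives the same treatment estimate for either. The cost is a sentence or two in the plan and slightly more analysis work. The patient scales need no new data.

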## Discussion

The concept of family mediated exercise therapy is not a new phenomenon. It is common practice in rehabilitation of children with neurological impairments [45]. While it cannot be denied that the sudden and profound effects of stroke on family roles and functioning create stress for the stroke survivor and their families, the available evidence suggests that carers and families want information and want to be more fully involved in their rehabilitation [46,47]. It is also evident that more therapy is of benefit to people with stroke and the aim of this RCT is to maximise motor recovery by allowing the patient to practice activities with his/her family outside of the routine treatment hours. The qualitative data will allow the researchers a deeper insight into the impact of the programme of the patient and his/her family. Only by establishing evidence-based interventions, such as the one outlined in this protocol, can we strive to reduce the impact of this illness on the individual, the family and society.
